#### Imaging

Standing radiographs of the cervical spine in neutral, flexion, and extension will be performed preoperatively and at 1, 2, and 5 years of follow-up. When radiographs of the neutral position are executed, the participant will be in a comfortable standing position with the head facing forward for a horizontal gaze. The radiographs will be used to investigate the sagittal alignment by measuring the C2–C7 Cobb angle, C2–C7 cSVA, C7 slope, and T1 slope [16].

MRI of the cervical spine with T1- and T2-weighted images in sagittal and T2-weighted in axial planes will be performed preoperatively, after 3 months and at 5 years of follow-up. Hereby the compression of the spinal cord can be assessed as well as the performed decompression and the degenerative development over time.

Computed tomography (CT) will be performed pre- and postoperatively and at 3 months and 5 years to control the screw fixation, bony anatomy, and fusion (Table 2).

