## Statistical methods

### Statistical methods for primary and secondary outcomes {20a}

All endpoints will be analyzed in the modified intention to treat (mITT) population, defined as randomized patients who are still alive without having emigrated or left the study after 2 and 5 years.

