#### Secondary outcomes

The secondary outcomes will be analyzed using ordinal regression models, adjusted for sex. In addition, each secondary endpoint will be dichotomized and analyzed using logistic regression. The dichotomization will be done by comparing baseline and follow-up data, either based on MCID when applicable or else by defining success as an improvement from baseline. All secondary endpoints will be analyzed at 1, 2, and 5 years of follow-up, but not until the study is closed.

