### Methods in analysis to handle protocol non-adherence and any statistical methods to handle missing data {20c}

Dropouts may be one out of two entities: (1) the participant actively leaves the study or (2) the participant has died or does not show up on follow-ups for unclear reasons. In case 1, the participant will not be part of the study anymore and data will not be retrieved from other information sources. In case 2, information about living participants will be retrieved from the medical records, radiographs, and the Swedish patient registry. In case 2, missing PROMs will be imputed using multiple imputation [44]. Reoperations, adverse events, and radiographs will not be imputed.

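### Missing radiographs are left unimputed and no model links the visits, so the 5-year alignment comparison loses some precision that the scheduled 1- and 2-year films could restore

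*Protocol article*

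**What the plan says.** The section on non-adherence and missing data {20c} separates participants who actively leave from those who die or stop attending. For living non-attenders, information is retrieved from medical records, radiographs and the patient registry, and missing PROMs are multiply imputed. The section then closes with "Reoperations, adverse events, and radiographs will not be imputed".

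Under Statistical methods, Secondary outcomes: "The secondary outcomes will be analyzed using ordinal regression models, adjusted for sex". Each endpoint is also dichotomized and analysed by logistic regression, and "All secondary endpoints will be analyzed at 1, 2, and 5 years of follow-up, but not until the study is closed".

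Outcomes {12} lists change from baseline in cSVA and C2–C7 Cobb angle at 5 years. Under Imaging: "Standing radiographs of the cervical spine in neutral, flexion, and extension will be performed preoperatively and at 1, 2, and 5 years of follow-up". The analysis population is "defined as randomized patients who are still alive without having emigrated or left the study after 2 and 5 years".

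**The concern.** The two kinds of outcome are treated differently, and radiographs get the weaker treatment. PROMs go out by post (section {18a}), whereas a standing radiograph needs a visit, and the abstract describes these patients as often frail. Retrieval from records cannot supply a film that was never taken. A living participant still in the study but without a 5-year film therefore drops out of the 5-year alignment comparison, even with films from before surgery and from years 1 and 2.

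The endpoint has weight despite being secondary. The background names progressive kyphotic deformity as a specific risk of muscle-preserving laminectomy, and the hypothesis in Objectives {7} is that laminectomy alone does as well without delayed kyphosis. A reoperation result favouring laminectomy would be read beside this comparison. Leaving reoperations and adverse events unimputed is reasonable, because they are events that can be traced in records and the registry. An unmeasured angle or distance cannot be.

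**Working it through.** **Inputs from the protocol.** 300 randomised 1:1, 5-year mortality 16.3%, a further 5% lost to dropout and emigration, 236 analyzable. The last figure reproduces: 300 × (1 − 0.163 − 0.05) = 236.1, or 118 per arm. These losses lie outside the analysis set, so they say nothing about how many survivors lack a film. The protocol gives no figure for missing films, for the SD of alignment change or for the correlation between visits.

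**Assumptions.** SD of change 10 mm; share without a 5-year film m = 5–30%, reference 20%; correlation between 2- and 5-year change ρ = 0.5–0.8, reference 0.8. The calculation is for a difference in means. The planned ordinal regression works on another scale, so the relative loss carries over only approximately.

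**Precision, films missing at random.**
- All films present: SE = 10 × √(2/118) = 1.302 mm.
- Available 5-year films only: the variance is multiplied by 1/(1 − m). At m = 0.2 this is 1.25, so SE = 1.302 × √1.25 = 1.456 mm.
- With the 2-year film: the variance is multiplied by 1 + [m/(1 − m)](1 − ρ²). At m = 0.2 and ρ = 0.8 this is 1 + 0.25 × 0.36 = 1.09, so SE = 1.302 × √1.09 = 1.359 mm.
- Gain: 1 − 1.359/1.456 = 6.6% smaller SE; 1.25/1.09 = 1.147, worth about 15% more films.

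| Missing | SE, available films (mm) | SE with 2-year film, ρ = 0.5 | ρ = 0.7 | ρ = 0.8 |
|---|---|---|---|---|
| 5% | 1.336 | 1.327 | 1.319 | 1.314 |
| 10% | 1.372 | 1.355 | 1.338 | 1.328 |
| 20% | 1.456 | 1.419 | 1.382 | 1.359 |
| 30% | 1.556 | 1.497 | 1.437 | 1.399 |

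At 5–10% missing and ρ = 0.8 the gain is only about 2–3% of the SE.

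**Bias, by simulation with 118 per arm and absence depending on the 2-year value.**
- *Same mechanism in both arms* (ρ = 0.8, log-odds slope 1.0 per SD, true difference 3.0 mm, about 24–27% missing): mean estimate 2.83 mm from available films and 3.03 mm using the 2-year film. The bias of about 0.2 mm is small against an SE of 1.46 mm. With a slope of 0.8, ρ = 0.7 and about 20% missing, the bias is about −0.01 SD at a true difference of 0.3 SD and about zero at no difference.
- *Absence related to alignment in the laminectomy arm only* (slope 0.8, ρ = 0.7, about 20% missing): bias −0.10 SD at no true difference and −0.12 SD at 0.3 SD, that is 1.0–1.2 mm at SD 10 mm, in favour of laminectomy. Using the 2-year film brings it to about zero. With the slope at 1.0 and about 23–27% missing, available films estimate a true 3.0 mm as 1.2 mm (ρ = 0.8) to 1.4 mm (ρ = 0.7).

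**The case against.** Four points are fair.

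*The loss is modest and its size is assumed.* This stands. The documents give no missing-film rate, and at 5–10% missing there is little to recover.

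*The article does not say that visits are fitted separately or that earlier films are ignored.* This stands as a limit: the absence of a longitudinal model is inferred from the secondary-outcome section, and a condensed article may leave model structure to the analysis plan. The no-imputation rule, however, is stated outright, and nothing described offsets it.

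*A reader might infer that the kyphosis comparison is biased because deformed or frail patients stay away.* The documents do not support that. Such absence distorts the level of kyphosis in each arm, but the arm difference hardly moves unless the mechanism differs by arm. Unblinded participants make a difference possible, not established. Its direction is also open, since patient-initiated assessment for pain or deformity and films retrieved from records could over-represent symptomatic patients.

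*A reader might extend the point to Nurick grade, grip-and-release and foot-tapping, or want symptom-prompted films discarded.* Neither follows. The no-imputation sentence does not name those measures, and their listed endpoint is at 2 years. The protocol does not say why retrieved films were taken, and dropping them could throw away observed late deformity, leaving a model to predict those patients from earlier, milder films.

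The primary endpoint is untouched: kyphosis that leads to reoperation counts there.

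**Conclusion.** The point holds as a modest, easily mended weakness in a secondary analysis. The stated rule, with no described model across visits, limits the 5-year alignment comparison to participants with a 5-year film. In the reference case (20% missing, SD 10 mm, ρ = 0.8) the SE is 1.46 mm instead of 1.36 mm; the gap narrows with fewer missing films or weaker correlation. Bias in the arm difference is about 0.2 mm on a true 3 mm if absence works alike in both arms. It reaches about 0.1 SD or more only if alignment-related absence differs by arm. Using earlier films removes that bias only as far as absence depends on what those films show.

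**What to change.** Take radiographs out of the no-imputation sentence and do one of the following:
- include cSVA and C2–C7 Cobb angle, with their baseline, 1- and 2-year values, in the multiple imputation already planned for PROMs, keeping the planned ordinal regression; or
- analyse each in one repeated-measures model of the scheduled films, with baseline as covariate and visit-by-arm terms, reading the contrast at 5 years.

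Keep reoperations and adverse events unimputed. Keep retrieved films, but flag unscheduled ones for a sensitivity analysis. Report the available-film analysis alongside, and state how films taken after revision surgery are counted.

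The cost is a change of wording, slightly more programming and reliance on a missing-at-random assumption. No new data are needed, and because secondary analyses wait until the study is closed, the change can be made beforehand.

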### Plans to give access to the protocol, participant-level data, and statistical code {31c}

A deidentified dataset and the R code used for the statistics will be delivered upon request after the completion and publication of the 5-year follow-up.

### Composition of the data monitoring committee, its role, and reporting structure {21a}

Data monitoring is performed on a weekly basis by the main coordinator and controller with the support of the local coordinator to ensure that all events, PROMs, and radiology are performed according to the protocol.

The data monitoring committee comprises the study director and the main coordinator and controller. The monitoring committee is independent from sponsors and competing interests.

### Adverse event reporting and harms {22}

As reoperations due to complications and adverse events are the primary outcome, all adverse events in both groups will be recorded. The adverse events will be graded according to severity (categorical variable): grade 1, any non-life-threatening complication treated without invasive procedures; grade 2, complications requiring invasive management such as surgical, endoscopic, and endovascular procedures; grade 3, life-threatening adverse events requiring treatment in an intensive care unit; and grade 4, death as a result of complications [41].

The adverse events are reported by the senior spine surgeon to the steering committee.

### Frequency and plans for auditing trial conduct {23}

Auditing trial conduct will be performed by the independent observer, and an interim analysis will be made when 100 participants are included.

### Plans for communication of important protocol amendments to relevant parties (e.g., trial participants, ethical committees) {25}

Any change in the protocol from the primary protocol that is approved by the Swedish Ethical Review Authority must be resubmitted for ethical approval and reported to relevant parties such as trial participants and trial registries.

### Dissemination plans {31a}

The trial result will be submitted to peer review journals and presented at international meetings.

## Discussion

Cervical spondylotic myelopathy is the most common cause of spinal cord dysfunction in the elderly worldwide [1]. In the twentieth century, laminectomy was regarded as the standard posterior approach for the treatment of CSM but fell into disfavor due to reports of postlaminectomy kyphosis in the 1970s and 1980s [25]. Since then instrumentation techniques for spinal fixation and fusion have developed and spine research has become an industry-driven field [45]. Posterior laminectomy is now commonly combined with prophylactic fusion even in patients with a lordotic cervical spine [12]. Laminoplasty was developed as a motion-preserving technique for posterior decompression in patients with CSM [46]. The technique retains the facet integrity as well as preserves the extensor muscles and has equal or better results compared with posterior laminectomy and fusion [47]. These comparisons indicate that it is not the laminectomy itself that may lead to postoperative kyphosis but the damage to other important structures like muscles and facet joints. With a technique to spare these structures, instrumentation may be redundant. The research group of [name] has described the posterior muscle-preserving selective laminectomy technique and observed that the patients maintain sagittal balance after surgery without any progression of kyphosis [16]. However, the technique has not been subjected to any well-designed clinical trials.

The term “instability” has been defined as “loss of the spine’s ability to maintain its patterns of displacement under physiologic loads so there is no initial or additional neurologic deficit, no major deformity, and no incapacitating pain” [48]. The cutoff values most commonly used to realize this description into practice are a translational movement of > 3.5 mm, an angulation of > 11°, and < 50% facet joint covering on flexion-extension radiographs [23]. Thus, when Panjabi and White wrote these cutoff values in the 1970s, their cadaver studies described trauma to the cervical spine, not degenerative changes. Specific cutoff values for “instability” in the nontraumatic degenerated cervical spine are yet to be defined.

The anterior versus posterior decompression and fusion approaches have been compared without showing any differences in postoperative results [12, 13]. The anterior approach is often preferred to restore sagittal alignment [25]. As in the lumbar spine, the loss of lordosis may be a compensatory mechanism to create more space in the narrowed spinal canal. After decompression, the conditions are reversed and the lordosis may be restored as long as the muscles and the facets are preserved [16]. Thus, adding fusion to the decompression surgery would be unnecessary. Nonetheless, a modified K-line INT < 4 mm has been observed to be disadvantageous for a posterior approach and thus needs to be regarded as a guideline cutoff value [22].

Until now, there is no consensus on whether to fuse or not when laminectomy is performed, and the choice of surgical method is dependent on the surgeon’s preference. This will be the first randomized controlled trial comparing two common surgical treatments for CSM: the posterior muscle-preserving selective laminectomy and posterior laminectomy with instrumented fusion.

## Trial status

The trial started in February 2022 with four sites in Sweden, the Department of Surgical Sciences, the Academic University Hospital in Uppsala; the Department of Neurosurgery, Karolinska University Hospital in Stockholm; the Neuro-Orthopaedic Center, Ryhov Hospital in Jönköping; and the Department of Orthopaedics, Sahlgrenska University Hospital in Gothenburg. More sites may be recruited during the enrollment phase. The expected enrollment is 5 years, and the conclusion of the study is estimated at 10 years.

## Data Availability

Access to decrypted data and safekeeping of the decryption key will be limited to the principal investigator and the study nurse. Participating spine surgeons only have access to their own site data and cannot see the data of the other recruiting centers. The use of encrypted data sets and the RedCap software management program will protect confidentiality. Anonymized data can be provided upon request.

## Abbreviations

ASP: Adjacent segment pathology
BMI: Body mass index
CI: Confidence interval
CSM: Cervical spondylotic myelopathy
cSVA: Cervical sagittal vertical axis
CT: Computed tomography
DISH: Diffuse idiopathic skeletal hyperostosis
EQ-5D: European Quality of Life Five Dimensions
HADS: Hospital Anxiety and Depression Scale
HIV: Human immunodeficiency virus
ITT: Intention to treat
K-line INT: Kyphosis-line minimum interval distance
MCID: Minimal clinically important difference
MRI: Magnetic resonance imaging
NDI: Neck Disability Index
NRS: Numeric Rating Scale
OPLL: Ossification of the longitudinal ligament
P-mJOA: Patient-derived modified Japanese Orthopaedic Association scale
PP: Per protocol
PROM: Patient-reported outcome measure
REDcap: Research Electronic Data Capture
SD: Standard deviation
Swespine: Swedish spine registry
